## **1. Overview**

### **1.1 Study Information**

Project Title: Study of usefulness of ePRO in cardiovascular disease

Ethics Review Committee Approval Number: 20221093

UMIN ID: UMIN000049251

### **1.4 Contracted Facilities**

None

## **2. Background of Study**

### **2.1 Background, study objective and meaning**

#### **2.1.1 Background**

The number of cardiovascular patients is rapidly increasing as the population ages. In particular, the number of patients with heart failure is on the rise worldwide (1).

According to the epidemiological survey by Japanese Cardiology Society, the number of heart failure hospitalization has been increased by 10,000 per year and the prevalence of heart failure is about 1,000,000 persons today. The number of HF patients in Japan will continue to increase (2).

In the patients with cardiovascular disease such as HF, atrial fibrillation (AF) and coronary artery disease (CAD), behavioral pattern in life, daily activity, quality of sleep and mental state have a significant impact on their disease condition (3-5).

For modifying their lifestyle and preventing disease progression, it is vital to assess Patient-Reported Outcome (PRO) that can quantify symptom, physical function, anxiety, satisfaction and so on.

The principal aim in the management of cardiovascular disease in recent years has extended beyond merely reducing cardiovascular events; it has also encompassed enhancing the quality of life for individual patients. PRO measures (e.g. Kansas City Cardiomyopathy Questionnaire (KCCQ), Atrial Fibrillation Effect on Quality-of-life (AFEQT) and Seattle Angina Questionnaire (SAQ)) and Short Physical Performance Battery have been regarded as important endpoints in clinical research (6).

We previously established multicenter registries for patients with cardiovascular disease, collecting PROs using disease-specific questionnaires (7) and reported the importance of PRO assessment in clinical settings. From this registry, we found that discrepancies in symptom recognition between patients and physicians often existed in daily practice (8). Furthermore, physicians' under-recognition of patients' symptoms was associated with less aggressive treatment, such as catheter ablation (9,10). It is imperative to develop the electronic PRO (ePRO) survey system utilizing IoT for implementing PRO assessment in clinical practice.

As ePRO becomes more widespread, it is expected that medical care, which was often viewed as a service provided unilaterally by doctors, will be transformed into a service that enables mutual communication between doctors and patients.

#### **2.1.2 Study Objective**

To investigate whether visualizing patient health status with ePRO monitoring for cardiovascular patients improve patient satisfaction.

### **2.1.3 Meaning**

Discrepancies in recognition between patients and physicians in healthcare have been reported both domestically and internationally to affect the quality of care and treatment outcomes. Therefore, it is important to understand this discordant recognition between patients and physicians, and as a foundation, it is necessary to understand the patient perspective in clinical practice. Traditionally, healthcare has often been perceived as a service provided unidirectionally from the physician's side, but with the spread of ePRO, the patient perspective is becoming visible, transforming healthcare into a service that enables bidirectional communication between patients and physicians. Additionally, by reducing the omission of patients' subjective symptoms, earlier and more appropriate therapeutic interventions can be expected. It is also characteristic of ePRO that it includes items such as anxiety about treatment and satisfaction, and understanding these aspects may lead to a more holistic clinical practice that comprehensively understands and values the patient's values and quality of life (QoL).

### **2.2 Previous evidence and validity of the Research Implementation**

Concordant understanding of disease condition and treatment choice is necessary for the improvement of the quality of care and treatment success. We have previously reported that the discordance in recognition of symptoms between patients and physicians often existed in daily practice. One of the supportive methods for shared understanding of patient health status between patients and physicians is the implementation of ePRO, which can make patient information visible to physicians.

The routine collection of ePRO is recommended with a Class I indication in the European Society of Cardiology guidelines. We have previously introduced PROs into disease registries for heart failure, atrial fibrillation, and angina pectoris, emphasizing the importance of making treatment decisions based on patient-reported health status. There is a discrepancy between the symptoms perceived by patients and those recognized by physicians, resulting in the insufficient provision of advanced but invasive medical care (8,9). A previous study in the field of oncology have also reported that the implementation of PRO assessment improved outcomes (1), and verification of this in the field of cardiology remains a critical issue.

For the implementation of PROs, which quantify (numerically measure) patient-reported symptoms in medical care, the development of digitized ePROs utilizing IoT is essential. We have advanced the development of digital versions of the AFEQT for atrial fibrillation, the

KCCQ for heart failure, and the SAQ for stable angina, which have been previously employed in the cardiovascular disease domain. Using these prototypes, we conducted a pilot study with 10 patients. As a result, we received positive feedback from patients, such as being able to convey information they couldn't fully express during consultations and having a clearer understanding of whether their clinical course was proceeding successfully.

### **2.3 Participant Risk and Benefit**

**Risk:** There is no financial burden. The time required for ePRO and questionnaires is approximately 5 minutes. In the event of adverse events, appropriate medical care will be provided. Participant privacy is respected through linked anonymization. The participant list is password-protected by the information manager, stored on a hard disk, and kept in the Sports Medicine Center office. Specifically, personal information such as the participant's name and medical record number, as well as ePRO and questionnaire results obtained using wearable devices, will be accessed and viewed through the dedicated website for this study. This allows for conversations between physicians and participants regarding trends during consultations, contributing to the improvement of patient satisfaction verified in this study. Researchers can then download and anonymize the data for storage and use within the office's hard disk as anonymized research data.

Only authorized research personnel and maintenance developers of this study system with access rights to website for this trial can register and have access to the personal data of participants. There is no risk of privacy infringement because all downloaded research data undergo anonymization processing.

**Benefits:** The results of ePRO are calculated immediately and visualized on the device, allowing the current scores to be shared between physicians and subjects during consultations. There is no compensation for participation in this study.

### **2.4 Compliance with Regulations and Guidelines**

The research will be conducted in accordance with the Helsinki Declaration and ethical guidelines for biomedical and medical research involving human subjects.

### **2.5 Target Patient**

Refer to Section 5 for criteria for selection, exclusion, and discontinuation of subjects

### 4. Study Design

#### 4.1 Outcome

##### (1) Primary Outcome

Patient satisfaction calculated by Likert-Scale

(2) Secondary outcome

Assessment of well-being, patient preferences for shared decision-making using questionnaires.  
Qualitative assessment of ePRO monitoring in ePRO group.

(3) exploratory outcome

Factors associated with improved patient satisfaction in ePRO group

## 4.2 Study method

In this study, participants will be randomly assigned to ePRO monitoring or usual care. We will explain this research face-to-face to the patients and obtain electronic consent. Prior to randomization, patients with HF, AF or CAD will be assigned to KCCQ-12, AFEQT or SAQ respectively. For patients with two or more of these three coexisting cardiovascular diseases, treating physicians will assign an appropriate PRO measure based on their primary cardiovascular disease.

Participants will be randomly assigned to ePRO group or control group. After randomization, they are instructed to respond to the questionnaires for outcome assessment. Patients assigned to ePRO group are also asked to respond to physician assigned PRO measures.

All patients will be followed up on an outpatient basis every 4 weeks ( $\pm 2$  weeks) for a total of 5 visits. At every visit, patients in the ePRO group will receive a smart tablet and answer for the assigned questionnaire (KCCQ-12, AFEQT or SAQ) before entering the examination room. The reports of PROs will be displayed on smart tablets and shared between physicians and patients during medical examination. Patients in the control group received standard care in accordance with the latest clinical guidelines. All patients will be asked to respond to the questionnaires for outcome assessment at the fifth visit

In addition, the following information will be collected from participants through interviews or electronic medical records:

- (1) Patient information: the date of birth, age, sex, height, weight, Vital signs (systolic blood pressure, diastolic blood pressure, heart rate, respiratory rate), family history, past history of illness, medication history.
- (2) Blood tests: White blood cell count (WBC), red blood cell count (RBC), hemoglobin concentration (Hb), hematocrit value (Ht), mean corpuscular volume (MCV), mean corpuscular hemoglobin (MCH), mean corpuscular hemoglobin concentration (MCHC), platelet count (PLT),

Total protein (TP), creatinine (CRE), uric acid (UA), sodium (Na), potassium (K), chloride (Cl), calcium (Ca), aspartate aminotransferase (AST), alanine aminotransferase (ALT), gamma-glutamyltransferase ( $\gamma$ -GT), alkaline phosphatase (ALP), lactate dehydrogenase (LDH), total cholesterol (Tcho), triglycerides (TG), LDL cholesterol (LDL-cho), HDL cholesterol (HDL-cho), non-HDL cholesterol (calculated value), total bilirubin (T-BIL), glucose (GLU), HbA1c, brain natriuretic peptide (BNP), NT-proBNP, Prothrombin time-international normalized ratio (PT-INR), Activated partial thromboplastin time (APTT), D-dimer.

- (3) Electrocardiogram
- (4) Echocardiography
- (5) Endoscope test
- (6) Imaging tests (computed tomography, magnetic resonance imaging, radioisotope imaging, chest X-ray (presence of pleural effusion, CTR)
- (7) Exercise test

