### **4.3.2 Data Collection**

Data will be collected using electronic devices (e.g. smart tablets) for PRO and questionnaires. These data will be collected five times during consultations (every 4 weeks  $\pm$  2 weeks). Patient background information will be obtained directly from the subjects, and medical information will be gathered from electronic medical records.

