#### **4.4 Bias**

Adaptive randomization method will be applied to reduce intervention bias. Due to the nature of the intervention, blinding is not feasible, and thus the trial will be conducted with an open-label design.

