#### **4.6 Enrollment and Registration of Study Participants**

- (1) Confirm that candidate patients meet all inclusion criteria and do not meet any exclusion criteria.
- (2) Provide an explanation of the study and obtain consent electronically.
- (3) Assign an anonymized ID to subjects who have given consent. Randomly determine whether the subject will respond to ePRO or not on a computer before starting the study.

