### **1.1. Primary endpoint**

Patient satisfaction calculated by Likert-Scale

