## **6. Efficacy Analysis**

### **6.1. Primary endpoint**

Patient satisfaction calculated by Likert-Scale. Patient satisfaction, assessed using a Likert scale were compared between the two groups. Mean changes from baseline to the final follow-up were analyzed using unpaired t-tests.

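### Baseline is undefined, and the only first outcome questionnaire described comes after open-label randomisation, so knowledge of the allocation can enter the primary change score

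*Combined protocol and SAP*

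**What the plan says.** Protocol 4.2 and SAP 3 give the same sequence: explanation and electronic consent, choice of the disease-specific measure, randomisation, outcome questionnaires, then five outpatient visits.

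- Before allocation, the only questionnaire step is the choice of instrument: "Prior to randomization, patients with HF, AF or CAD will be assigned to KCCQ-12, AFEQT or SAQ respectively". No outcome questionnaire is described at that stage.
- After allocation: "After randomization, they are instructed to respond to the questionnaires for outcome assessment".
- Protocol 4.6 also puts allocation ahead of study start: "Randomly determine whether the subject will respond to ePRO or not on a computer before starting the study".
- The final assessment is fixed: "All patients will be asked to respond to the questionnaires for outcome assessment at the fifth visit".
- Protocol 4.4 states that "blinding is not feasible, and thus the trial will be conducted with an open-label design".
- The primary endpoint is "Patient satisfaction calculated by Likert-Scale", and SAP 6.1 says of it: "Mean changes from baseline to the final follow-up were analyzed using unpaired t-tests". SAP 6.2 applies the same method to the PSQ and QoI scores.

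Neither document defines baseline. Neither says when a patient learns the allocation. Neither states whether, at the first visit, the outcome questionnaire comes before or after the first ePRO report is shared. Protocol 4.3.2 gives a different schedule for PRO and questionnaire data ("These data will be collected five times during consultations"), but that also contains no measurement before allocation.

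**The concern.** A baseline taken before allocation cannot be influenced by it, so arms differ at baseline only by chance. A baseline taken after an open allocation loses that protection. Satisfaction is a self-rating, and a patient pleased to receive ePRO, or disappointed not to, may answer differently on that account. This is response bias in one of the two measurements that make up the endpoint.

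The direction depends on how patients react. A higher ePRO baseline or a lower control baseline leaves ePRO less room to show improvement and hides benefit. A lower ePRO baseline or a higher control baseline creates apparent benefit. An observed baseline difference could not be attributed to chance or to reaction, because the data do not separate the two. Since the trial's purpose is to find out whether ePRO monitoring improves satisfaction, error in either direction matters.

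**Working it through.** **The plan's own figure.** SAP 1.5 gives 25 × 2 = 50, which agrees. Protocol 9.1 and SAP 1.5 state that no power or sample size calculation was made, so there is nothing further to reproduce.

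**Inputs from the documents.** 25 per arm (SAP 1.5), two-sided 5% level (SAP 2.4), unpaired t-test on change (SAP 6.1).

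**Assumed inputs.** The documents do not give these: equal SD of the score at both times (set to 1), baseline-to-final correlation ρ of 0.3 to 0.7, baseline shift s of 0.2 to 0.5 SD in one arm, and the fraction k of that shift still present at visit 5.

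**Bias.** With no true effect, if the ePRO baseline is raised by s and ks persists at visit 5, the expected between-arm difference in change is ks − s = −(1 − k)s. With k = 0 it is −s; with k = 1 it is 0.

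**Rejection rate.** SD of change = √(2(1 − ρ)). The standardised bias is d = (1 − k)s / SD of change. The t statistic has 48 degrees of freedom, noncentrality d√(25/2) and critical value 2.011.

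For s = 0.3 and k = 0:
- ρ = 0.3: SD of change 1.183, d = 0.254, noncentrality 0.896, rejection 14.2%.
- ρ = 0.5: SD of change 1.000, d = 0.300, noncentrality 1.061, rejection 18.0%.
- ρ = 0.7: SD of change 0.775, d = 0.387, noncentrality 1.369, rejection 26.9%.

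Rejection rates under no true effect, no carry-over (nominal 5%):

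| Shift (SD) | ρ = 0.3 | ρ = 0.5 | ρ = 0.7 |
|---|---|---|---|
| 0.2 | 9.0% | 10.7% | 14.6% |
| 0.3 | 14.2% | 18.0% | 26.9% |
| 0.5 | 31.0% | 41.0% | 60.9% |

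A simulation of 40,000 trials at ρ = 0.5 gave 17.6% for a shift of 0.3 and 41.4% for 0.5.

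**Carry-over.** With k = 0.5 and ρ = 0.5, shifts of 0.2, 0.3 and 0.5 act as 0.10, 0.15 and 0.25, and rejection falls to about 6%, 8% and 14%.

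**Direction.** At ρ = 0.5, s = 0.3 and k = 0, 17.9 of the 18.0 percentage points lie in the direction of the bias and about 0.1 in the other. If the ePRO baseline is raised, these are false findings in favour of control.

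**Adjustment.** Analysis of covariance on the same baseline would leave a bias of about −ρs with no carry-over: −0.15 SD for s = 0.3 and ρ = 0.5. That reduces the problem without removing it.

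**The case against.** The strongest reply is that the shift is hypothetical. No document reports one, and an open-label design does not fix the moment at which a patient is told the allocation. The text also describes the post-randomisation questionnaires before it describes the visits with ePRO reports, which suggests, without guaranteeing, that the first rating precedes the first report. All of this stands. A reader might infer that patients certainly rate their baseline knowing their arm, or after exposure to ePRO. The documents support only that nothing prevents either.

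Second, the same pleasure or disappointment may persist to visit 5, and what persists cancels in the change score. This also stands: it is why the bias is (1 − k)s, and a reader should not assume that every baseline shift passes through in full.

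Third, this is a 50-patient pilot with no power target, and reordering leaves the visit-5 rating unblinded. Both are true and limit the weight of the point. But a 5% test is still planned, and a biased pilot estimate would misinform any later trial.

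Fourth, the bias may be conservative. That holds only if patients welcome ePRO. Patients reluctant to use it would push the other way.

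**Conclusion.** The point holds as a structural defect. Baseline is undefined, the only candidate measurement follows open-label allocation, and no step keeps knowledge of the allocation or the first ePRO report away from it. The primary endpoint and the PSQ and QoI changes are all exposed.

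The size is unknown. The illustrative range for a 0.3 SD shift is 14% to 27% rejection under no effect with no carry-over, and about 8% with half carry-over at ρ = 0.5. These figures rest on the assumed SD, correlation, shift and carry-over, not on anything in the documents.

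Two stronger readings are not supported. One is that the trial suffers selection bias: nothing in this sequence disturbs the random allocation itself, and the issue is how a known allocation may colour a response. The other is that the order inflates false claims of benefit: if patients welcome ePRO, nearly all the excess rejections favour control.

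**What to change.** In protocol 4.2 and 4.6 and SAP 3, set the order as eligibility, electronic consent, baseline outcome questionnaires, then release of the allocation. Smart-Pro already handles consent and allocation (protocol 6.1) and stores the questionnaire data (protocol 7.2), so it can hold the allocation until the baseline form is submitted. In SAP 6.1 and 6.2, define baseline as the score submitted before allocation is released, and so before any ePRO report is shown. Reconcile protocol 4.3.2 with 4.2 on when outcome questionnaires are given.

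The study period in protocol 4.7 ends on March 31, 2024, so patients may already have been enrolled under the present order. In that case, report when the first rating was taken relative to allocation and to the first ePRO report, and add a sensitivity analysis comparing visit-5 scores between arms without using this baseline.

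The cost is a reordering of existing steps and a wording amendment, with no extra visit or questionnaire. A patient who leaves between the form and allocation leaves one unused form. Neither the new order nor the visit-5 comparison removes open-label bias in the visit-5 rating, and the report should say so.

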## **4.3 Data**

### **4.3.1 Original data**

Data will be collected from electronic PRO survey, questionnaire for outcome assessment and electronic medical records.

### **4.3.2 Data Collection**

Data will be collected using electronic devices (e.g. smart tablets) for PRO and questionnaires. These data will be collected five times during consultations (every 4 weeks  $\pm$  2 weeks). Patient background information will be obtained directly from the subjects, and medical information will be gathered from electronic medical records.

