## **7. Efficacy Evaluation**

### **7.1 Efficacy Evaluation Indicators**

### **7.2 Methods for Evaluating, Recording, and Analyzing Efficacy Evaluation Indicators**

ePRO and questionnaire data will be collected using electronic devices and stored in the Smart-Pro (tentative name) system on servers contracted by Chubu Electric Power Co., Inc. The data will be displayed on a dedicated web interface to improve patient satisfaction through result viewing during consultations between physicians and patients. Researchers will extract data from the server and manage it as research data. The data will be matched with patient background and medical data, and changes in the utilization of ePRO will be analyzed. Planned analyses include paired t-tests and logistic regression analyses.

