## **2.7. Data Handling**

In principle, data handling decisions will be made by the Principal Investigator. If questions or uncertainties arise, the final decision will be made in consultation with the Lead Statistician. The handling of missing values and variable transformations is outlined below:

- **Missing Data:** No special statistical imputation methods will be applied to missing data. An unpaired t-test will be performed on complete data excluding missing data.
- **Outlier Data:** The handling of outlier data will be determined by the Data Handling Committee (comprising the Principal Investigator and the Lead Statistician).
- **Variable Transformation:** If variable transformations (e.g., square root or logarithmic transformations) are applied, details will be documented in the "Analysis Results Report."

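### The protocol gives two schedules for the outcome questionnaires and lets questionnaire results be viewed in consultations, so the primary satisfaction score needs one schedule, a defined final follow-up and protection from the treating physician

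*Combined protocol and SAP*

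**What the plan says.** **Schedule.** Protocol 4.3.2 opens with "Data will be collected using electronic devices (e.g. smart tablets) for PRO and questionnaires" and continues "These data will be collected five times during consultations". It exempts no arm and no instrument. Protocol 4.3.1 treats the two kinds of data as separate sources: "Data will be collected from electronic PRO survey, questionnaire for outcome assessment and electronic medical records".

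Protocol 4.2 describes a different schedule, and SAP 3 repeats it. At the start, "After randomization, they are instructed to respond to the questionnaires for outcome assessment". At the end, "All patients will be asked to respond to the questionnaires for outcome assessment at the fifth visit". What happens at every visit is the KCCQ-12, AFEQT or SAQ, in the ePRO group only, answered before the patient enters the examination room.

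**Analysis.** SAP 6.1: "Mean changes from baseline to the final follow-up were analyzed using unpaired t-tests". SAP 2.7 applies no imputation: "An unpaired t-test will be performed on complete data excluding missing data". SAP 4.1 removes subjects without efficacy data from the full analysis set. Protocol 5.3 foresees that questionnaire collection may be stopped for a patient. No early-termination assessment is described.

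**Display.** Protocol 7.2 speaks of ePRO and questionnaire data together and then says: "The data will be displayed on a dedicated web interface to improve patient satisfaction through result viewing during consultations between physicians and patients". Protocol 2.3 likewise has ePRO and questionnaire results viewed on the study website to support conversation in the consultation. Protocol 4.2 mentions sharing only the PRO reports.

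**The concern.** The primary endpoint is a change in a satisfaction score, so the plan must fix when the score is taken, which post-baseline value counts, and who sees the answer.

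Two analysts who follow different sections would build different data sets. One would have five scores per patient and would have to decide what to do with the interim ones. The other would have two scores and would lose every patient who stops before visit 5. With 25 patients per group, a few such patients matter.

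The display wording raises a second issue. Protocol 4.4 makes the trial open-label, and satisfaction with care is a subjective rating. If the treating physician can see it, patients may rate more kindly than they feel, and there is no reason to expect this to be equal in the two arms.

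**Working it through.** **1. The two schedules side by side.**

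| | Protocol 4.3.2 | Protocol 4.2 and SAP 3 |
|---|---|---|
| Outcome questionnaires per patient | 5 | 2 (start, visit 5) |
| Post-baseline scores, completer | 4 (visit 1 as baseline) | 1 |
| Post-baseline scores, patient who stops after visit 3 | 2 | 0 |
| Final follow-up in SAP 6.1 | visit 5 or last available score | visit 5 |
| Use of interim scores | not stated | none exist |

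Section 4.2 does not use the word only. That is inferred from its naming the fifth visit for the outcome questionnaires while giving every-visit collection to the disease-specific instruments.

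**2. Could 4.3.2 mean only the disease-specific instruments?** Section 4.3.1 lists the ePRO survey and the outcome questionnaire separately, which argues against it. Even on that reading 4.3.2 is wrong for controls, who do not answer those instruments. It needs correcting either way.

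**3. Precision (illustrative).** The plan has no figure to reproduce: the sample size of 50 rests on feasibility, with no SD, effect size or dropout rate. Assumptions: five visits, unit variance at each, no baseline difference between arms, and 20% monotone loss spread evenly (5% with baseline only, 5% last seen at each of visits 2, 3 and 4, 80% complete). Let r be the correlation between visits 1 and 5. It equals the adjacent-visit correlation under compound symmetry (CS) and its fourth power under AR(1). Large-sample variance of the visit-5 estimate per arm, times the number randomised in the arm:

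- complete-case change score: 2(1 − r)/0.8
- complete-case ANCOVA: (1 − r²)/0.8
- baseline-adjusted mixed model: the visit-5 diagonal element of the inverse information, summed over dropout patterns, given baseline

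| Structure, adjacent correlation | r | Change score | ANCOVA | Mixed model | Change / mixed | ANCOVA / mixed |
|---|---|---|---|---|---|---|
| CS 0.5 | 0.500 | 1.250 | 0.938 | 0.9134 | 1.37 | 1.03 |
| CS 0.7 | 0.700 | 0.750 | 0.638 | 0.6140 | 1.22 | 1.04 |
| CS 0.8 | 0.800 | 0.500 | 0.450 | 0.4311 | 1.16 | 1.04 |
| AR(1) 0.5 | 0.0625 | 2.344 | 1.245 | 1.2225 | 1.92 | 1.02 |
| AR(1) 0.7 | 0.240 | 1.900 | 1.178 | 1.1307 | 1.68 | 1.04 |
| AR(1) 0.8 | 0.410 | 1.476 | 1.040 | 0.9842 | 1.50 | 1.06 |

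The excess is 16% to 37% under CS and 50% to 92% under AR(1). The last column isolates the interim visits: 2% to 6%. The rest is baseline adjustment, where change score over ANCOVA is 2(1 − r)/(1 − r²) = 2/(1 + r). Even in the smallest case (CS 0.8), 2/1.8 = 1.11, so 11 of the 16 points come from baseline adjustment.

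**4. Loss of patients alone.** The 95% confidence interval half-width, in SDs of the analysed score, is t × √(2/n). With 25 per group it is 2.011 × √(2/25) = 0.57. With 20 per group (20% loss) it is 2.024 × √(2/20) = 0.64.

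**The case against.** **The operative schedule is clear.** Section 4.2 and SAP 3 agree, whereas 4.3.2 is a short logistics paragraph that plausibly merges two data streams. Under 4.2 there is one post-baseline assessment, so final follow-up can only be visit 5. This stands, and it is why correcting 4.3.2 is the simplest repair. It does not remove the conflict or supply the missing definition.

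**The variance figures mostly concern another choice.** This stands too. A reader might infer from the 16% to 92% that the schedule conflict costs that much precision. It does not: ANCOVA on the two-time schedule recovers most of it, and the schedule accounts for 2% to 6%.

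**Selective dropout.** A reader might infer that dissatisfied ePRO patients will leave and that the complete-case test will then favour ePRO by a known amount. The documents give no dropout rate and no sign of who would leave. As an example, suppose 80% of the lowest quartile at visit 4 leave, in the ePRO arm only. The loss is 20%, and the mean of those who stay shifts at visit 4 by 0.2 × 1.271/0.8 = 0.318 SD. The bias in mean change is that shift times (correlation of visits 4 and 5 minus correlation of visits 4 and 1). Under AR(1) at 0.8 this is 0.318 × (0.8 − 0.512) = 0.09 SD. Under compound symmetry the two correlations are equal and it is zero.

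**Courtesy bias.** A reader might also infer that patients rate their physician in the physician's presence. The documents do not say so. The reference in 4.3.2 to consultations can mean at the visit, and 4.2 has the ePRO instruments answered before the examination room. What is supported is narrower: 2.3 and 7.2 let questionnaire results be viewed in consultations, and nothing exempts the satisfaction score.

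**Conclusion.** The inconsistency is real and touches the primary endpoint. Protocol 4.3.2 conflicts with 4.2 and SAP 3 on how often the outcome questionnaires are taken. SAP 6.1 does not define final follow-up, which becomes ambiguous if 4.3.2 governs. Under 4.2, patients who stop early drop out of the primary comparison. Separately, 2.3 and 7.2 leave the satisfaction score open to the treating physician's view, against the narrower sharing in 4.2.

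The size is conditional. The gain available from using the baseline score and all visits is 16% to 92% of variance across the assumed structures, and most of it needs no change to the schedule. Bias from selective dropout or courtesy is possible in direction, but its size cannot be set from the documents. The precision figures also assume a baseline unaffected by allocation. Section 4.2 takes the first outcome questionnaire after randomisation, so this holds only if knowing the allocation does not move the first score.

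**What to change.** 1. State one outcome-questionnaire schedule for both arms in protocol 4.2, 4.3.2 and SAP 3. The simplest course is to correct 4.3.2 to match the other two.
2. Define final follow-up in SAP 6.1 as visit 5.
3. State in protocol 2.3 and 7.2 that outcome-questionnaire answers are not shown on the consultation display or to the treating physician, and that only KCCQ-12, AFEQT and SAQ reports are.
4. In SAP 6.1, replace the unadjusted change-score t-test with a comparison of visit-5 satisfaction adjusted for the baseline score (ANCOVA), and align SAP 2.7 and protocol 9.2. If interim scores are collected, use a baseline-adjusted mixed model with the visit-5 difference as primary.

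**Cost.** Wording, a display setting and minor analysis work. Items 2 and 4 need no new data. If five collections are chosen instead, patients in both arms answer the outcome questionnaires at visits 2 to 4 as well. On the protocol's figure of about 5 minutes per session (2.3 and 8.1), that is up to 3 × 5 = 15 minutes per patient, for an interim-visit gain of 2% to 6% of variance under the assumptions above.
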